Notably, the COVID-19 pandemic may have influenced the distribution of births in Dar es Salaam, which has likely led to an overall decrease of facility-births [7,43]. No Tanzanian data currently exist about possible COVID-19-related indirect consequences. Yet, modelling studies and emerging data from other LLMICs indicate how focusing resources to fight COVID-19 can further debilitate frail health systems and counteract improvements for maternity care, including raised maternal and perinatal mortalities [7,44]. In addition, introducing user fees for childbirth in the three regional referral hospitals in October 2019 might have influenced the distribution of births in the city. User fees entail that all women must pay 1–3 USD on admission as well as 11–32 USD for vaginal birth and 22–87 USD for CS. Women pay the lowest prices when they are referred from other facilities. The difference to the district hospitals is, however, partly balanced as women are expected to bring supplies for their birth or give a contribution (17–30 USD), which may not be required in the regional referral hospitals. There are, furthermore, additional fees in all five facilities for laboratory investigations, and for medications not available in the hospital. Notably, 90% of the Tanzanian women (age 15–49 years) in urban areas do not have any health insurance coverage [45]. Possibilities exist, however, for exemptions when women cannot afford fees or purchases.

Irrespective of potential declines in facility births, preliminary data indicate that the five study sites remain typical examples of overburdened, urban maternity units in LLMICs; they primarily serve women of lower socioeconomic status who live below the international poverty line, and each birth attendant is typically expected to attend to at least three to six labouring women simultaneously [11,30].

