#### III. Intervention implementation and evaluation

The overall implementation design will be a pragmatic stepped-wedged cluster-randomised trial with the five maternity units divided into three clusters receiving the intervention at cluster-level [50]. In a random order generated by R (R Core Team, 2017), maternity units will receive the intervention in three-month intervals. After enrolling in the third cluster, the intervention and evaluation will continue for additional nine months in all five sites (Figure 3).

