##### Evaluation of direct health outcomes

Our primary direct health outcomes are perinatal survival (stillbirths with positive foetal heart upon admission and pre-discharge neonatal mortality during the first seven days among inborn babies weighing ≥1000 g) and potentially avoidable CSs (by criterion-based case file review of care preceding surgery). Our secondary direct health outcomes include additional perinatal indicators (perinatal deaths divided into 1000–1999 g and ≥2000 g, first 24 hours pre-discharge neonatal mortality, Apgar score <7, admission to neonatal intensive care unit), maternal indicators (death, postpartum haemorrhage, uterine rupture, postpartum hysterectomy), and mode of birth (spontaneous vaginal birth, vacuum extraction, CS). In addition, background characteristics will be recorded for all women (age, parity, previous perinatal death, date and time of admission and birth, and birthweight). Sociodemographic indicators such as marital, economic, and educational status are not available in birth registries.

Birth outcomes and mode of birth will be prospectively measured from baseline and until nine months after the PartoMa intervention is implemented in the last facility. Thus, data collection will be ongoing for 18 months (Figure 3). Data will be gathered twice a week on each of the five study sites, primarily from the intrapartum birth register. Key indicators will be cross-checked with the antenatal, surgical, neonatal and postnatal wards registers and with the death certificate counter book. For each study site, data will be double entered every fifth week to ensure that the accuracy of data retrieval remains above 95%. Women referred to the study sites prior to birth from non-study health facilities will be included, but their clinical care prior to admission will not be possible to assess. When referrals occur from one to another study site, data will be recorded on where the woman gave birth. Babies referred postpartum for intensive care will be recorded at the facility where the woman gave birth (Table 1).

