### Data analyses

Overall analyses of the situational findings, co-creation, and implementation processes and effectiveness rely heavily on mixed-methods evaluation. This will include a broad spectrum of designs, from sequential explanatory and exploratory methods to embedded and converging triangulation designs [61].

Concerning the quantitative components, descriptive analyses will be performed in all five facilities as cluster-units of analysis. QoC provision and experience indicators (pre-selected, non-ambiguous criteria) and birth outcomes will be analysed and compared both within and between facilities using mixed effects logistic regression. Differences in seminar attendance and seminar return rates between maternity units will be compared using logistic regression. Knowledge scores are modelled as longitudinal data and compared over time using linear mixed-effects regression. Effects on each outcome will be reported as an average effect across facilities and its significance will be determined by likelihood ratio tests. Possible differences in effect between facilities will be investigated by incorporating a random slope regression model, reported by its standard deviation along with facility-specific deviations from the total effect. Possible time-dependence of the intervention (e.g. delayed entry) is investigated by allowing its effect to depend on facility-specific time since implementation and by adjusting for seasonality patterns. Additional adjustments for covariates will also be performed, such as for staff and patient counts, availability of essential supplies, other competing interventions or unintended events in the facilities, national holidays, maternal characteristics, and referral patterns. Both unadjusted and adjusted results will be reported. A biostatistician in the study team will closely supervise statistical analyses. All summary statistics and effect sizes will be reported along with 95% Wald-based confidence intervals, and statistical significance will be set at 5% level.

The qualitative analysis plan is presented separately [32].

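### The time terms named for the average intervention effect omit calendar period, so a common background trend would carry into the perinatal-death estimate

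*Protocol article*

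**What the plan says.** The section III. Intervention implementation and evaluation describes a "pragmatic stepped-wedged cluster-randomised trial with the five maternity units divided into three clusters receiving the intervention at cluster-level". The order is random and "maternity units will receive the intervention in three-month intervals". On what follows the last crossover, the same section states: "After enrolling in the third cluster, the intervention and evaluation will continue for additional nine months in all five sites". Under Evaluation of direct health outcomes: "Thus, data collection will be ongoing for 18 months".

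Data analyses names mixed effects logistic regression for birth outcomes and quality-of-care indicators. "Effects on each outcome will be reported as an average effect across facilities and its significance will be determined by likelihood ratio tests". A random slope covers differences between facilities. Time appears in one sentence, on possible time-dependence of the intervention, which is to be examined "by allowing its effect to depend on facility-specific time since implementation and by adjusting for seasonality patterns". The further covariates are staff and patient counts, supplies, competing interventions or unintended events, holidays, maternal characteristics and referral patterns. Calendar period and secular trend are not among them. Unadjusted and adjusted results will both be reported.

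Power calculation gives 80% power for a 22% relative reduction in intrahospital perinatal deaths (RR 0.78), by simulation, with details in Supplementary file S1.

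**The concern.** In a stepped-wedge trial every site's intervention data come later than its control data. The randomised order helps only if sites that have crossed over are compared with sites that have not, in the same calendar period. That requires a calendar-period term. Time since implementation describes how the effect develops after crossover. Seasonality describes a pattern that repeats each year. Neither represents a background change running through the 18 months.

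An analyst who followed the text as written would credit to the intervention a background fall in perinatal mortality, or let a background rise hide a benefit. The interval would also be too narrow for the question asked. The article gives reason to take calendar time seriously: Study setting discusses how focusing resources on COVID-19 can "counteract improvements for maternity care, including raised maternal and perinatal mortalities", and says that "introducing user fees for childbirth in the three regional referral hospitals in October 2019 might have influenced the distribution of births in the city".

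**Working it through.** **Inputs from the article.** Five sites in three clusters, three-month steps, nine further months and 18 months in total give six quarters. Crossovers fall at months 3, 6 and 9. The nine to 15 months of evaluation mentioned under Key Methodological Strengths and Limitations agrees: 18 − 3 = 15 and 18 − 9 = 9.

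**Assumed inputs.**
- The split of sites over clusters is not in the text, so 2-2-1, 2-1-2 and 1-2-2 were all tried.
- Deaths per site-quarter are not given; 72 is used. About 60,000 births a year / 5 sites / 4 quarters = 3,000 births, and 3,000 × 24 per 1,000 = 72. On the article's power premise (half of stillbirths, plus about as many neonatal deaths) the rate equals the overall stillbirth rate, taken here as about half of the quoted urban perinatal rate of 47 per 1,000.
- The trends of 5% and 10% per year are illustrative, and the 5% test is taken as two-sided.

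**The plan's own figure.** The 80% power cannot be reproduced, because the deaths per block and the simulation model are in the supplement. The side figures agree: 1 − 0.22 = 0.78 and 39/59 = 0.66.

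**Step 1: distance in time.** Mean control and intervention quarters are 1 and 4 for the first cluster, 1.5 and 4.5 for the second, and 2 and 5 for the third. The gap is 3 quarters in each.

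**Step 2: share of a linear log-trend entering the effect** (log-linear model with site effects, equal information per cell):

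| Time term | Quarters of trend absorbed | Variance factor v |
|---|---|---|
| None | 3.0 in all three splits | 0.154 to 0.171 |
| Quarter of year | 3.1 to 3.2 | 0.178 to 0.203 |
| Calendar quarter | 0 | 0.577 to 0.652 |

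**Step 3: apparent RR with no true effect and no time term** = (1 − yearly fall)^(3/4).
- 5% per year: 0.95^0.75 = 0.962.
- 10% per year: 0.90^0.75 = 0.924.
- With quarter of year added, about 0.96 and 0.92.

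**Step 4: standard error (SE) of the log RR** = √(v / 72).
- No time term: √(0.154/72) = 0.046 to √(0.171/72) = 0.049.
- Calendar quarter: √(0.577/72) = 0.090 to √(0.652/72) = 0.095.

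**Step 5: false-positive rate without a time term** (2-2-1, SE 0.049) = Φ(b/SE − 1.96) + Φ(−b/SE − 1.96), where b is the size of the log RR bias.
- 5% per year: b = 0.0385, b/SE = 0.79, about 12%.
- 10% per year: b = 0.079, b/SE = 1.62, about 37%.
- Simulation at 72 deaths gave 13.7% and 36.2%, and 4.7% and 5.0% with calendar quarter in the model.
- At 30 to 60 deaths the rates were 8 to 10% and 16 to 34% without a calendar term, and about 5% with it.

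**Step 6: deaths per site-quarter needed for 80% power at RR 0.78** = v × (2.80 / ln 0.78)².
- Equal counts in all cells: 20 to 22 with no time term, 73 to 83 with calendar quarter.
- Exposed cells reduced by 22%: 22 to 24 and 85 to 96.

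**Step 7: outcomes collected only at baseline and in months 7 to 9.** Control data fall in quarter 1 (common baseline) or quarters 1 to 3 (rolling baseline), and intervention data in quarters 4 to 6. No calendar quarter contains both. With site and calendar-quarter effects in the model, adding the intervention term does not raise the rank of the design matrix, so its effect is not identifiable.

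**Step 8: a single coefficient with calendar quarter included.** Under 2-2-1 it weights exposure quarters 1 to 5 by 1.04, 0.26, 0.00, −0.13 and −0.17. Suppose the effect builds up as RR 1.00, 0.88, then 0.78. The log RR is 0.26 × ln 0.88 − 0.30 × ln 0.78 = −0.033 + 0.075 = 0.041, so the reported RR is 1.04.

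**The case against.** The strongest reply is that a condensed article need not list every fixed effect. One paragraph covers all outcomes, the sentence on time concerns how the effect varies after roll-out, and the supplement or a statistical analysis plan may include period effects. Unadjusted may mean only without the listed covariates. The comparison runs within and between facilities, and covariates such as competing events, staffing and referral patterns would take up part of a trend. The power figure may even point to a calendar-adjusted simulation, since 73 to 96 deaths per site-quarter under that model is closer to the assumed 72 than the 20 to 24 needed without a time term.

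Much of this stands, and it limits the point. A reader might infer that the trial will certainly be analysed as a plain before-after comparison. The article does not establish that. A reader might also infer that it forecasts a mortality trend. It does not: the COVID-19 passage rests on modelling and other countries and says that no Tanzanian data exist, while the user fees predate the trial and are linked to where births take place.

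The reply does not remove the point. The article does choose time terms and a covariate list, and calendar period is in neither. A generous reading of seasonality as a quarter-of-year term in the main model leaves 3.1 to 3.2 quarters of trend in the effect. The covariates are no dependable substitute for period effects. With thousands of births per site, the between-facility part of the comparison adds almost nothing.

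**Conclusion.** The point holds for perinatal deaths and the other continuously collected birth outcomes. Followed as written, the model carries about 3 quarters of any common trend into the average effect, or RR of about 0.96 or 0.92 under assumed falls of 5% or 10% per year. The 3-quarter figure follows from the article's timetable and held in every split tried. The size of any trend, the 72 deaths and the false-positive rates are illustrations.

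Two stronger conclusions are not supported. The stated power cannot be called wrong, because the model and counts behind it are not shown; it needs confirming. Nor does it follow that the time-since-implementation model should supply the main result. With calendar quarter included, its average over five exposure quarters has an SE of about 0.20 to 0.23 at 72 deaths per site-quarter, which gives only about 19 to 24% power at RR 0.78.

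**What to change.** - State calendar quarter (or month) as a fixed effect in the main model for perinatal deaths and the other continuously collected birth outcomes, including the version reported as unadjusted. If the supplement or analysis plan already does so, say so under Data analyses.
- Confirm that the 80% power at RR 0.78 was simulated under that model, and restate it if not.
- Keep the time-since-implementation model as a pre-stated sensitivity analysis. Note that a constant-effect coefficient with period effects can misreport an effect that builds up.
- Label the avoidable-caesarean co-primary and the experience-of-care outcomes as before-after comparisons. No model term can change this with the present collection windows.

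Cost: the main change is to the analysis text and needs no new data. The SE of the log RR roughly doubles, from 0.046–0.049 to 0.090–0.095 at the assumed 72 deaths per site-quarter. If the power simulation left out calendar time, the restated power will be lower.

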## Abstract

While facility births are increasing in many low-resource settings, quality of care often does not follow suit; maternal and perinatal mortality and morbidity remain unacceptably high. Therefore, realistic, context-tailored clinical support is crucially needed to assist birth attendants in resource-constrained realities to provide best possible evidence-based and respectful care. Our pilot study in Zanzibar suggested that co-created clinical practice guidelines (CPGs) and low-dose, high-frequency training (PartoMa intervention) were associated with improved childbirth care and survival. We now aim to modify, implement, and evaluate this multi-faceted intervention in five high-volume, urban maternity units in Dar es Salaam, Tanzania (approximately 60,000 births annually). This PartoMa Scale-up Study will include four main steps: I. Mixed-methods situational analysis exploring factors affecting care; II. Co-created contextual modifications to the pilot CPGs and training, based on step I; III. Implementation and evaluation of the modified intervention; IV. Development of a framework for co-creation of context-specific CPGs and training, of relevance in comparable fields. The implementation and evaluation design is a theory-based, stepped-wedged cluster-randomised trial with embedded qualitative and economic assessments. Women in active labour and their offspring will be followed until discharge to assess provided and experienced care, intra-hospital perinatal deaths, Apgar scores, and caesarean sections that could potentially be avoided. Birth attendants’ perceptions, intervention use and possible associated learning will be analysed. Moreover, as further detailed in the accompanying article, a qualitative in-depth investigation will explore behavioural, biomedical, and structural elements that might interact with non-linear and multiplying effects to shape health providers’ clinical practices. Finally, the incremental cost-effectiveness of co-creating and implementing the PartoMa intervention is calculated. Such real-world scale-up of context-tailored CPGs and training within an existing health system may enable a comprehensive understanding of how impact is achieved or not, and how it may be translated between contexts and sustained.

Trial registration number: NCT04685668

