Adding further to the complexity of providing maternity care in congested, resource-constrained facilities, urban birth attendants increasingly must manage an alarming double burden of co-morbidities, including infectious and cardiovascular-metabolic diseases. In 2016, 62% of the urban women still perceived malaria and HIV/AIDS as the most serious health problems in Tanzania. Simultaneously, urban women increasingly suffer from obesity, hypertension, and diabetes; 42% of the urban women in Tanzania are overweight (body mass index ≥25) versus 21% of their rural counterparts [35,41]. On top of this, the majority of COVID-19 cases occur in urban settings [35,42].

The PartoMa Scale-up Study will be conducted in five of Dar es Salaam’s government-owned maternity units, which provide comprehensive obstetric and neonatal care: Mwananyamala, Amana and Temeke are regional referral hospitals and Sinza and Mbagala Rangi Tatu are district hospitals (Figure 2). In 2019, they had been the five highest volume maternity units for more than a decade (annual average of 13,116 births per facility), and they jointly cared for approximately 40% of all urban and sub-urban births in Dar es Salaam [33]. These five sites enable a robust stepped-wedge design (please see power calculation below). At the same time, it was estimated to be realistic, considering the study’s available resources and the desire for more in-depth analysis.

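### The blanket rule of Wald intervals for all summary statistics breaks down for facility-level proportions of very rare secondary outcomes; sparse proportions should be excepted

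*Protocol article*

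**What the plan says.** The Data analyses section of the protocol article fixes the interval method for everything reported: "All summary statistics and effect sizes will be reported along with 95% Wald-based confidence intervals". No exception follows. The same section says that "descriptive analyses will be performed in all five facilities as cluster-units of analysis" and that birth outcomes will be "compared both within and between facilities using mixed effects logistic regression". For the average effect on each outcome, "its significance will be determined by likelihood ratio tests", and "statistical significance will be set at 5% level". Differences in effect between facilities are handled by a random-slope model.

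Under Evaluation of direct health outcomes, the secondary outcomes include "maternal indicators (death, postpartum haemorrhage, uterine rupture, postpartum hysterectomy" among others.

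The article does not say whether the Wald interval for a proportion is built on the proportion or the log-odds scale. It does not say over what period facility-level maternal outcomes will be summarised, and it gives no rate for rupture or hysterectomy.

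**The concern.** The Wald interval for a proportion relies on a normal approximation that fails when only a handful of events is expected. Uterine rupture and postpartum hysterectomy may well be that rare within one hospital, and the first hospitals to start contribute only three control months. With no event in that period, the prescribed method gives either an interval from 0 to 0 or no interval at all.

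One primary outcome is potentially avoidable caesarean sections, so severe maternal outcomes are a natural check on harm. The article plans no interim analysis of severe adverse events, so the final tables carry that check. A baseline interval of zero width in such a table would claim certainty that the data do not give.

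**Working it through.** **The plan's own figures.** The article states no coverage figure and no expected count for any maternal outcome, so there is nothing to reproduce. Its one power figure (80% at a relative risk of 0.78) concerns perinatal deaths and does not bear on this point.

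**Inputs from the document**
- Births per facility and quarter: the Abstract has "approximately 60,000 births annually" over five units, so 60,000 / 5 / 4 = 3,000. Study setting has "annual average of 13,116 births per facility", so 13,116 / 4 = 3,279. At a given expected count the two denominators give the same coverage to 0.1 point.
- Control time: 18 months of data, three-month steps, and nine months after the last start. The clusters therefore start after 3, 6 and 9 months, with about 3,000, 6,000 and 9,000 control births per facility.
- The only maternal rates given: 432 (urban) and 336 (rural) deaths per 100,000 live births, from Study setting. They are population figures, not rates for the five sites.

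**Assumption.** Rupture or hysterectomy at 0.3 to 1 per 1,000 births, which is 0.9 to 3 expected events in 3,000 births.

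**Formulas**
- Wald: p̂ ± 1.96 × √(p̂(1 − p̂)/n).
- Probability of no event: (1 − p)^n.
- Exact coverage: the sum of the binomial(n, p) probabilities of all counts x whose interval contains p.

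**Single intervals at n = 3,000 (per 1,000 births)**
- 0 events: Wald 0 to 0; Wilson 0 to 1.28. On the logit scale the Wald interval is undefined.
- 1 event: Wald −0.32 to 0.99; Wilson 0.06 to 1.89.
- 3 events: Wald −0.13 to 2.13; Wilson 0.34 to 2.94.

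**Coverage of nominal 95% intervals at n = 3,000**

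| Rate per 1,000 | Expected events | P(0 events) | Wald | Wilson |
|---|---|---|---|---|
| 0.3 | 0.9 | 41% | 59% | 94% |
| 0.5 | 1.5 | 22% | 78% | 93% |
| 0.7 | 2.1 | 12% | 88% | 94% |
| 0.9 | 2.7 | 7% | 93% | 94% |
| 0.98 | 2.94 | 5% | 94% | 97% |
| 1.0 | 3.0 | 5% | 80% | 97% |

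The drop between the last two rows comes from the discreteness of the counts. The Wald interval for one event ends at 0.987 per 1,000, so it contains 0.98 but misses 1.0. At 1.0 both x = 0 and x = 1 miss. Below that point nearly all the loss is the zero-event case: at 0.3, 1 − 0.41 = 0.59.

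On a fine grid of rates from 0.3 to 1 per 1,000, Wald ranges from 59% to 94%, Wilson from 92% to 98%, and Clopper-Pearson stays at or above 97.5%.

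**Longer periods, same assumed rates.** On the same grid, Wald covers about 79% to 95% at 6,000 and at 9,000 births, and about 88% to 95% at 18,000.

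**Maternal death at the documented rates.** At 432 per 100,000, expected deaths are 3,000 × 0.00432 = 13.0 (14.2 at 3,279 births) and Wald coverage is 94% (93%). At 336 per 100,000, expected deaths are 10.1 (11.0) and coverage is 93% (91%).

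**Effect scale.** Take a log odds ratio within one facility between a three-month and a nine-month period (3,279 and 9,837 births, same rate). With 1, 2 and 3 expected events in the shorter period, it cannot be estimated in 40%, 14% and 5% of cases. Where it can be estimated, Wald coverage is 97% to 99%.

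**The case against.** The case for leaving the rule alone has several strands.

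- *The denominator is the worst available.* Only the first cluster has a single control quarter, and the article does not promise facility-by-quarter intervals for rupture or hysterectomy. This stands: that table is an assumption, and longer periods reduce the problem considerably.
- *The scale is not stated.* Birth outcomes are modelled by logistic regression, and on the log-odds scale limits are never negative. This stands for the zero-width statement, which holds on the proportion scale only. It does not rescue the rule, because at zero events the logit interval does not exist.
- *The inference is protected.* Effects are judged by likelihood ratio tests and differences between facilities by a random-slope model. This stands. A reader might infer that degenerate intervals would make a later event look like a real rise, or produce false differences between hospitals in the hospital-level fallback analysis. The article plans no such comparison of raw facility intervals, and that fallback is a theory-based, mixed-methods analysis that mentions no intervals for rare maternal events.
- *An article leaves such detail to the analysis plan.* This lowers the weight of the point but does not remove it, because the sentence positively prescribes a method for all summary statistics.

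A reader might also infer that coverage is 60% to 80% for the rare maternal outcomes generally. The documents do not support that. Coverage is not monotone, and about 64% of the assumed range at 3,000 births gives more than 80%. Maternal death is adequately covered at the one documented rate, and no rate is given for haemorrhage.

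**Conclusion.** The point holds in a narrow form and is minor. The prescribed rule gives no usable interval when a facility-level proportion has zero events, and this needs no assumption about rates. How often it happens, and how poor coverage is otherwise, depends on two assumptions: a rate of 0.3 to 1 per 1,000, and a summary over one control quarter of about 3,000 births in the first cluster. Under both, zero events occur 41% to 5% of the time and proportion-scale Wald coverage lies between about 59% and 94%. With 6,000 or more births the range is roughly 80% to 95%.

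The documents do not support extending this to the trial's conclusions. Neither primary outcome and none of the likelihood ratio tests is shown to be affected. What is at stake is the honesty of the error bars on sparse descriptive proportions of secondary outcomes.

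**What to change.** Except proportions from the Wald rule: state that facility-level descriptive proportions will carry 95% Wilson or exact (Clopper-Pearson) intervals. Both give a usable interval at zero events.

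For effect sizes on sparse outcomes, profile-likelihood intervals would agree with the planned likelihood ratio tests. They do not cure everything: when a period has no events they are unbounded on one side, and the plan should say that they will be reported as such.

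The cost is one or two sentences and standard software options. The intervals become slightly wider or asymmetric, and Clopper-Pearson is conservative (coverage of at least 97.5% over the range examined at 3,000 births). No design element, outcome or test changes.
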